### Participant withdrawal

Participants in the study are free to withdraw from participating at any point, without giving a reason and without their legal rights or usual care being impacted. It is possible for a participant to with draw from receiving the therapy, but continue to remain in the trial for the follow up assessments, in essence, participants will be asked if they are willing to continue data collection assessments at 16 weeks and 28 weeks, if they wish to withdraw from the iMAPS intervention. While being reminded of their right to withdraw without giving a reason, we will politely ask if they are willing to give a reason, but remind them that this is entirely voluntary.

If continued participation for some reason is assessed by the researchers to be harmful in some way, then we may withdraw a participant. The Trial Steering Committee (TSC) which incorporates a Data Monitoring and Ethics function will review all instances of adverse events, regardless of whether they are judged to be attributable to the trial or interventions. Reviewing this information, the independent committee members will decide if a participant should be withdrawn from the study. All adverse events deemed related to study participation will be reported the Research Ethics Committee (See Section 9 for further details).

There is a possibility that individuals taking part may lose capacity to consent to continue participating in the study. In this event, we would pause their participation to see if they regain their capacity (acknowledging that capacity fluctuates in people with psychosis and may be temporary). However, if they continue to lack capacity, this may also mean they are no longer able to consent to ongoing participation in the study or for their data to be retained. In line with previous studies (including the iMAPS case series) we will seek informed consent in advance from all participants to retain their data if they subsequently withdraw because of loss of contact or are withdrawn by the study team due to loss of capacity

## Assignments of Interventions

**Allocation Concealment Mechanism**

## Allocation

**Sequence Generation**

Participants will be allocated in a 2:1 ratio to one of two arms within the RCT; usual care or iMAPS intervention plus usual care using blocks of random (but relatively short) length, stratifying by being a service user/patient under the care of a Community Mental Health Team or an Early Intervention Psychosis Team Health Teams (CMHT).

Allocation

Randomisation will be performed by SealedEnvelope, an online central randomisation service. The randomisation list will be generated by a statistician independent from the study team and held by SealedEnvelope

Delegated staff at sites with access to the online randomisation service will have to confirm the eligibility criteria before they enter the stratification information and being permitted to randomised. Then the system will allocate the randomised treatment which will be notified to the user via email. Allocation concealment (from both recruiting staff member and [potential] participant) will be ensured, as the system will not release the randomisation code until the participant has been randomised.

Participants will be allocated to one of two arms within the RCT, randomised (2:1) to usual care or iMAPS intervention plus usual care using blocks of random (but relatively short) length and implemented using the on-line sealedenvelope.com system. The parameters for the randomisation list using sealed envelope (<https://www.sealedenvelope.com/simple-randomiser/v1/lists>) will be prepared by [name] and [name] (e.g. treatment groups, block sizes, list length and stratification) however, the seed for the random number generator will be input by an independent statistician colleague at University of Manchester who is independent from the study team.

## (Allocation Implementation)

The responsibility for recruiting and randomising participants into the study lies with the Chief Investigator and staff at site with access to the online randomisation system which will be provided with a secure login to the sealedenvelope.com website.

## Blinding

To reduce detection bias, researchers undertaking assessments will be blind to the allocation. The success or otherwise of our attempts at blinding will be recorded. Where a research assistant is unblinded, another research assistant will make an appointment to undertake the assessment.

*Allocation concealment (from both recruiting staff member and [potential] participant) will be ensured, as the system will not release the randomisation code until the participant has been randomised which takes place after all baseline measurements have been completed*.

.

It is not anticipated that un-blinding of the research assistants will occur in the trial and it is not expected that there would be any reason for emergency un-blinding of the researchers. Any instances of unintentional un-blinding will be recorded.

The Trial Statistician will remain blinded to treatment allocation until after the Statistical Analysis Plan (SAP) have been sign off and the analysis of unblinded data commences.

## Outcome Measures (Feasibility, Clinical and Health Cost)

1. Recruitment rate (Number of participants consented into the trial and randomised. This will also include number of referrals per month; source of recruitment; number of patients (potential) participants contacted; number of participants screened for eligibility; number of screened patients who are found to eligible, reasons for non-eligibility or withdrawal of interest – where potential participants are happy to share these reasons).
2. Therapy Engagement % who drop out of therapy/% who did not receive treatment allocated. (This will include number of therapy sessions attended).
3. Therapist adherence to therapy protocols and supervision protocols. This will include assessing therapist fidelity against the Cognitive Therapy Rating Scale Revised (CTS-R) or the Cognitive Therapy Rating Scale for Psychosis (CTS-Psy) and the nested study developing an iMAPS fidelity scale (see Appendix 4).
4. Completion rates at week 0, 16 weeks and 28 weeks on widely used outcome measures of schema (Brief Core Schema Scales)(Fowler, Freeman, Smith, Kuipers, Bebbington, Bashforth, et al., 2006), imagery characteristics (VAS/MPIQ) (Holmes et al., 2016), and delusions (Psychotic Symptom Rating Scales; PSYRATS (Haddock et al., 1999)) and the overall measures completion rate. In line with guidance for feasibility trials, we have not specified a primary outcome, and in addition, the study seeks to identify a suitable primary outcome for the larger planned trial (Lancaster et al., 2004). Adverse events, quality of life and NHS service use will also be measured.
5. Standard deviations of normally distributed clinical outcomes
6. Reported breaks of assessor blinding, participant, and staff views on the trial acceptability (including randomisation) and possible changes to the intervention and trial protocol.
7. We will also include the EQ-5D 5L, a NICE recommended health measure utilised for QALY estimate and the ReQoL-10 for feasibility of economic analysis. We will record all service user and other relevant health economic data, using an adapted version of the Economic Patient Questionnaire (Davies, Lewis and Jones, 2007) which includes questions from the Client Service Receipt Inventory (CSRI).
8. Service users views regarding acceptability of i) participating in the trial and ii) of receiving iMAPS therapy assessed via qualitative interview. We will also interview a number of clinician colleagues about their experience of referring to the trial and feedback .
9. Health economic outcomes, via HE measures and service use questionnaire. A range of NHS and social care service use is collected, including inpatient admission, outpatient visits, A&E, primary, community and social care use.”
10. SAEs and AEs

**Full Trial Progression Criteria:**

We will progress to a full trial if we all our criteria below are classed as GREEN; if one or more is AMBER, we will investigate whether it is possible to make adjustments to the trial design to overcome any problems and, if that appears possible, progress to a full trial (including an assessment of the success of our adjustments in its internal pilot, where appropriate); if one or more is RED, we will not progress unless we can make the substantial amendments which would be necessary to make a full trial feasible.

1. Recruitment: GREEN: >=80% (n>=36) of target recruited; AMBER >=40 % (n=18-35)-< 80% of target recruited; RED <40% (n<18) of target recruited.
2. Retention: GREEN: >=80% of participants providing 16-week outcome data ; AMBER: >60%- <80% of

participants providing 16-week outcome data; RED: <60% of participants providing 16-week outcome data.

- 1. Adherence: GREEN>=75% adherence of participants attend at least 5 sessions of therapy, AMBER>=40% participants

attend at least 5 sessions of therapy; RED: <40% of participants attend at least 5 sessions of therapy (based on Jolley et al. 2015).

Assessment Measures

|  | **Procedures and Questionnaires** | **Mins** | **Baseline** | **16 Weeks Follow Up** | **28 Weeks Follow Up** |
| --- | --- | --- | --- | --- | --- |
|  | Demographics | 5 | X | As needed | As needed |
| **Psychosis Measures** | PANSS | 60 | X | X | X |
|  | PSYRATS | 15 | X | X | X |
|  | QPR | 5 | X | X | X |
| **Imagery** | Brief Imagery Interview  Visual Analogue Scales/MIPQ  Psychosis Imagery Questionnaire (PIQ) | 10  5 | X  X | X | X |
| **Schemas** | BCSS | 2 | X | X | X |
| **Trauma** | TALE | 5 | X |  |  |
|  | ITQ | 5 | X | X | X |
|  | BES | 5 | X | X | X |
| **Mental Health and Functioning** | BAI | 5 | X | X | X |
|  | CDS | 9 | X | X | X |
|  | WEMWBS | 5 | X | X | X |
|  | PSP | 10 | X | X | X |
| **Health Economics** | EQ-5D-5L | 2 | X | X | X |
|  | ReQoL-10 | 2 | X | X | X |
|  | Economic Patient Questionnaire | 10 | X | X | X |
|  |  |  |  |  |  |
| **Working Alliance** | WAI-client | 5 | 3^rd^ Session | 6^th^ | 9^th^ |
|  |  | 5 |  |  |  |
| **THERAPIST ONLY** | WAI-therapist | 5 | 3^rd^ Session | 6^th^ | 9^th^ |
|  | iMAPS therapy fidelity Checklist  CTS-R or CTS-Psy |  | A selection of therapy sessions will rated in supervision and by an independent external therapist |  |  |
| **Adverse Effects** | CGI-IP | 1 | Each Session |  |  |
|  | CGI-SP | 1 | Each Session |  |  |
|  | AEP | 5 |  | End of therapy or at dropout, if consent to send has been given in advance. |  |

Note: PANSS: Positive and Negative Syndrome Scale (Kay et al., 1987); PSYRATS: Psychotic Symptom Rating Scales(Haddock et al., 1999); QPR: Questionnaire about the Process of Recovery(Law et al., 2014); MIPQ: Mental Imagery in Psychosis Questionnaire/Visual Analogue Scales (Taylor et al., 2019); PIQ: Psychosis Imagery Questionnaire Taylor et al. 2022); BCSS, Brief Core Schema Scale (Fowler, Freeman, Smith, Kuipers, Bebbington, & Bashforth, 2006); TALE: Trauma and Life Events Checklist (Carr et al., 2018); ITQ: International Trauma Questionnaire (Cloitre et al., 2018); BES: Basic Emotions Scale (Power, 2006); BAI: Beck Anxiety Inventory (Beck et al., 1988); CDS: Calgary Depression Scale (Addington et al., 1993); WEMWBS: Warwick Edinburgh Mental Well Being Scale (Tennant et al., 2007); PSP: The Personal and Social Performance Scale (Morosini et al., 2000); EQ-5D-5L: The EuroQol 5-Dimenson 5 Level measure (Janssen et al., 2013); REQol-10: Recovering Quality of Life Measure (Keetharuth et al., 2018); Economic Patient Questionnaire (Shields et al., 2020); WAI-SR-client: Working Alliance Inventory – client version (Hatcher & Gillaspy, 2006); WAI-SRT-therapist: Working Alliance Inventory – therapist version(Hatcher & Gillaspy, 2006); CTS-R: Cognitive Therapy Rating Scale – Revised (Blackburn et al., 2001); Cognitive Therapy Scale for Psychosis (Haddock et al., 2001); Clinical Global Impression- Improvement Participant Version (CGI-IP) Clinical Global Impression - Severity Participant (CGI-SP) Version; Adverse Effects of Psychotherapy Questionnaire (Hutton, 2013)

We will also capture postcode and calculate the Index of Multiple Deprivation Decile by using the following website link:

<http://imd-by-postcode.opendatacommunities.org/imd/2019>

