## INTERVENTION

**iMAPS.** Therapists delivering the iMAPS therapy approach (Taylor et al. 2019) will be trained and supervised by lead \applicant and co-applicant experts in psychological therapy for psychosis to deliver the expanded 12 sessions of individualised, personalised iMAPS intervention over a twelve-week therapy phase. Please see our published iMAPS treatment approach journal publication for more details (Taylor et al 2019).

The therapy includes novel change techniques including imagery re-scripting (imaging an image or memory and changing the ending to change the meaning) of past events, imagery re-scripting of flash-forwards, working with nightmares and creating positive imagery. Other techniques used to work with negative core beliefs and images are i) learning that pushing images away makes them come back stronger (image suppression and responding differently), ii) testing beliefs about images and schemas (behavioural experiments), iii) changing (manipulation) of images and iv) working with upsetting memories. The use of the “Safe Place” image, as the first introduction to imagery work, ensures that patients have a personalised strategy to reduce any distress experienced. There are clear distress protocols developed and agreed in advance with patients (including managing dissociation) before the imagery sessions begin (after a careful assessment and formulation).

Please see more details in Table 1.**Table 1** Outline of the iMAPS Therapy (Taylor et al 2019)

Training and Supervision by CT, JK with support from KB, AA

Table 1. *iMAgery focused therapy for PSychosis (iMAPS)*

| Phase of Treatment | Main approach |
| --- | --- |
| Assessment, Goals, Psychoeducation | Interview  Imagery measures – Visual Analogue Scale, Spontaneous Use of imagery Scale (SUIS), Image Diaries, Assessing different types of imagery, Assessment of schema – core schema, early negative schema, schema modes |
| Formulation & Case Conceptualisation | Shared psychological formulation |
| Intervention |  |
| Imagery CT Approaches  Safe Place Image | A real or imaged safe place, described in detail, across each of the senses that gives a strong sense of safety and happiness |
| Image Suppression &  Behavioural Experiments | Similar to thought suppression experiments and behavioural experiments within other areas of CBT but with a focus on images |

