## Adherence and protocol deviations

### Adherence

Adherence to the intervention relies upon both therapist and participant factors.

a) Participant adherence

Participant adherence to the iMAPS-2 intervention will be measured by the number of therapy sessions attended by the participants allocated to the intervention arm. An individual will be classed as having attended a session if they attended a part or the whole of a session (defined as a minimum duration of 15 minutes). We will report the mean (SD) number of sessions attended or median (IQR), as appropriate. We will also summarise the number (%) of adherent participants with a 95% exact (binomial) confidence interval (for the %). If a participant attends 5 or more of the 12 sessions [4], then they will be deemed adherent.

b) Therapist fidelity

Therapist fidelity will be assessed by:

i) Rating a sample of audio recordings of therapy sess ions using the Cognitive Therapy Rating Scale Revised (CTS-R) or the Cognitive Therapy Rating Scale for Psychosis (CTS-Psy). Scale scores will be summarised as mean (SD) if they are (approximately) symmetrically distributed or median (IQR) if they are asymmetrically distributed.

ii) Therapists who are part of the research team (approximately 4 therapists) will complete the iMAPS fidelity scale after each therapy session to record the contents of each session in terms of: agenda targets; between-session activities/home tasks; the techniques used. Items within each domain of the fidelity scale will be summarised as follows:

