**Technique sessions (Yes, took place in session or NO, did not)**

1. Assessment and Engagement
2. Imagery Problem List
3. iMAPS Psychological Formulation (This could be with either the maintenance formulation, longitudinal formulation or both)
4. Psychoeducation regarding power of imagery
5. Normalising the image
6. Safe Place Image
7. Image Suppression
8. Behavioural Experiments
9. Upsetting Memories – Transformation
10. Upsetting Memories – Running image past the worst point
11. Upsetting memories – updating aspects of the image
12. Emotional bridge to past (diagnostic imagery exercise)
13. Imagery rescripting – past events
14. Imagery rescripting – flashforwards
15. Imagery rescripting – discussion of negative beliefs re self and others, schemas
16. Working with night-time imagery - Updating aspects of the image, rescripting new endings
17. Creating Positive Imagery – generating positive images

We will obtain the frequency (%) of all sessions by technique used.

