## Analysis populations

Feasibility analyses will include all the consented participants to estimate the proportion of eligible consented participants and eligible participants randomised. To summarise the number of iMAPS-2 therapy sessions attended, we shall include all the participants allocated to the intervention group. The proportion of adherent participants (attending at least 3 sessions of the iMAPS-2 therapy) will include all the participants allocated to the intervention group.

Analyses of efficacy will be by intention-to-treat (ITT), where all randomised participants for whom outcomes are available will be analysed in their allocated group regardless of their adherence to therapy.

The safety population will also follow the ITT principle and it will comprise all randomised participants.

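### Adherence counts attendance and technique use is summarised per session, so no analysis in the available text shows how many allocated participants received an imagery change technique

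*Combined protocol and SAP*

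**What the plan says.** **Adherence.** The progression criteria in protocol section 3.11 set the top level at "GREEN>=75% adherence of participants attend at least 5 sessions of therapy"; the amber and red levels use the same count. SHEAP 5.2 applies this to the individual: "If a participant attends 5 or more of the 12 sessions [4], then they will be deemed adherent". A session counts if the participant "attended a part or the whole of a session (defined as a minimum duration of 15 minutes". SHEAP 7.2, Objective 2, repeats the five-session rule over everyone allocated to the intervention and adds the proportion who received at least 300 minutes. None of these places sets a condition on content.

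**Order of therapy.** Protocol section 3.16 says distress protocols are agreed with patients "before the imagery sessions begin (after a careful assessment and formulation". Table 1 lists assessment, then formulation, then intervention, and section 3.16 presents the Safe Place image as the introduction to imagery work. No number of sessions is given for any phase.

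**Content.** Therapists "will complete the iMAPS fidelity scale after each therapy session to record the contents of each session". The record includes a yes/no list of 17 techniques, for which the SHEAP plans: "We will obtain the frequency (%) of all sessions by technique used". SHEAP 5.2 also plans session-level summaries of target image with agenda and of home tasks, summaries of image distress and functional impact, and CTS-R or CTS-Psy scores on a sample of recordings. Protocol sections 3.11 and 3.16 add fidelity ratings of a random selection of sessions, including with an iMAPS checklist.

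**The concern.** Objective 2 asks about engagement with and adherence to iMAPS, and adherence is one of three progression criteria. The criterion can be met by people who attended but had not yet reached the imagery change work. The one summary that records technique use has the session as its unit, so it cannot show how many people that describes.

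At stake is the design of the definitive trial and the treatment manual, both named as outputs in the protocol's objectives. The team would want to know how many allocated participants reached each technique, and at which session. A percentage of sessions answers neither question, although the raw records could.

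**Working it through.** **1. The plan's own threshold.** With 30 allocated to iMAPS, 75% is 0.75 × 30 = 22.5, so GREEN needs 23/30 = 76.7% (exact 95% CI 57.7% to 90.1%); 22/30 is 73.3%. With the 31 actually allocated (Supplementary Table 2), 0.75 × 31 = 23.25, so 24/31 = 77.4% (58.9% to 90.4%). The sample-size section gives a precision figure for retention only: 36/45 gives 65.4% to 90.4%, a width of 25.0%, as stated. The adherence criterion has no sample-size calculation of its own.

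**2. What the rule allows.** Five sessions at the minimum length come to 5 × 15 = 75 minutes, a quarter of the 300-minute summary (75/300 = 0.25). This is a floor, not a typical value: the text at Supplementary Figure 1 reports a mean of 495 minutes. Both figures measure time, not content.

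**3. Room for imagery work within five sessions.** If assessment and formulation take *m* sessions, a participant attending exactly five has 5 − *m* left. For *m* = 1, 2, 3, 4, 5 that leaves 4, 3, 2, 1, 0. The documents do not give *m*.

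**4. What a per-session percentage says about participants.** If a technique appears in *k* sessions and each person can have it in at most *s* sessions, the number of people who ever received it lies between *k*/*s*, rounded up, and the smaller of *N* and *k*. The session totals and percentages below are assumptions.

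| Assumption | Sessions *k* | *s* | Fewest people | Most people |
|---|---|---|---|---|
| 30 people, mean 9 sessions (270), 20% | 54 | 12 | 54/12 = 4.5 → 5 (17%) | 30 |
| Same, five sessions precede imagery work | 54 | 12 − 5 = 7 | 54/7 = 7.7 → 8 (27%) | 30 |
| 30 people, all 12 sessions (360), 25% | 90 | 12 | 90/12 = 7.5 → 8 (27%) | 30 |
| 23 people, exactly 5 sessions (115), 25% | 29 | 5 | 29/5 = 5.8 → 6 | 23 |

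The 5-of-30 bound needs five people to have the technique in 54 of their 60 sessions, leaving almost nothing for assessment and formulation. The 8-of-30 bound is the coherent one if five preparatory sessions are assumed. Either way the range is too wide to be useful.

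**5. Other participant-level figures.** Sessions attended, hours received and the 300-minute proportion measure quantity. SHEAP 6.3 plans the number receiving their allocated intervention, and protocol section 3.11 plans the percentage who did not receive it. Neither defines receipt by technique.

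**The case against.** The strongest reply is that attendance and content are separated on purpose. SHEAP 5.2 says adherence depends on both participant and therapist, measures the first by sessions attended and the second by fidelity, and takes the five-session rule from a cited source. That is a fair design, and nothing here requires the rule to change. It does not supply a count of people, however, because the content side is reported by session or from sampled recordings.

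Several stronger readings are tempting and should not be drawn:

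- **That the first five listed techniques fill five sessions with no imagery content.** The list is a set of tick-boxes, several of which can apply to one session, and it is not presented as a sequence. Items 2 to 5 (imagery problem list, iMAPS formulation, psychoeducation on imagery, normalising the image) are themselves imagery- or iMAPS-related.
- **That adherent participants commonly miss imagery work.** The rule permits it; the documents give no basis for saying how often.
- **That technique use is the only content summary.** Target image with agenda, home tasks and fidelity ratings are also planned.
- **That without this table a null 16-week estimate loses its meaning.** The trial is not powered for between-group differences (protocol section 3.21) and no formal testing is planned (SHEAP 5.1), so such an estimate could not show absence of effect in any case.

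The protocol also refers to an Appendix 4 on the nested fidelity-scale study, which is not in the text available. The protocol describes it as scale development, psychometric properties and use in evaluating therapists' adherence, which is not participant receipt. The point is nevertheless limited to the text that can be read.

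**Conclusion.** The gap is real and narrow. In the available text, adherence means five attended sessions of any content, technique use is planned only as a share of all sessions, and no analysis counts the allocated participants who received imagery change techniques. Under the assumed session totals, a per-session percentage leaves the number of recipients undetermined between roughly a fifth or a quarter of the arm and all of it. This does not invalidate the progression rule, and it does not show that imagery work went undelivered. It means that Objective 2 would be answered for attendance but not for receipt, although the data for receipt are recorded session by session.

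**What to change.** Leave the five-session progression rule and all per-session summaries as they are. In SHEAP 5.2 and under Objective 2 add one descriptive table over all participants allocated to iMAPS, giving number (%) with exact 95% CI for:

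- each technique: participants who ever received it, with the median session number of first use;
- at least one session with a pre-listed imagery change technique (items 7 to 17, plus Manipulation of Images, which is in protocol Table 1 but not in the SHEAP list, if it was recorded). Safe Place, item 6, should be shown separately, since one such session would otherwise satisfy the measure;
- at least one imagery rescripting session (items 13 to 16, or a stated reason for leaving out item 15);
- five or more sessions together with at least one change technique.

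Show the table beside the adherence result as context, not as a new criterion. Randomisation ended in September 2023 and results are attached, so if the analysis is complete the table should be labelled post hoc.

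In the same edit, reconcile SHEAP 5.3, which has "The proportion of adherent participants (attending at least 3 sessions of the iMAPS-2 therapy", with the five-session definition used elsewhere.

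The cost is SHEAP wording and a re-tabulation of session records already completed. The drawback is that the receipt figures may look less favourable than attendance.
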